**2.8 Outcome Measures:**

Note: all measures that involve participants walking will be conducted under remote supervision via Zoom.

***Primary Outcome:*** In contrast to medical interventions, many eHealth interventions have no pre-eminent outcome (e.g., reduced hypertension).66 Our primary outcome was selected to address the goals of the self-management program (patient perceived problems22, 67) identified in our previous work which is walking. We operationalized this as the Timed Up and Go Test (TUG), a performance measure of walking capacity -- deemed the strongest determinant of health-related quality of life and prosthetic walking proficiency in adults with LLA.68 It is widely used in intervention studies of the LLA population,69 with strong evidence of reliability, validity, and responsiveness.37, 70 The ability to walk longer distance permits people to explore and engage with their environment, which directly influences their choice of activities and social participation.71 Poor walking capacity may eventually lead to prosthetic abandonment.72 The Timed Up and Go (TUG) is a functional assessment that assesses aspects of mobility including the sit to stand transitions, gait initiation, acceleration and deceleration, and turning (Clemens et al., 2018). The TUG has been shown to be both a reliable and valid measure to evaluate how individuals with lower limb amputation function within their environment (Clemens et al., 2018). A mobile version of the TUG has also been shown to have excellent validity and reliability in the amputee population, making it an ideal tool for a mobile platform (Clemens et al., 2018). Participants will be asked to use a 48-cm-high armchair and mark a spot 3 meters from the front legs of the chair (Clemens et al., 2018). Participants would then be timed, starting from a sitting position, then standing and walking 3 meters, turning around and walking back and sitting back in the chair Clemens et al., 2018).

**Ambulatory Self-Confidence Questionnaire (ASCQ).** Perceived self-efficacy (confidence) includes the concept that one can exercise control over their health-related outcomes and activities and can therefore be an indicator in individuals perceived confidence in ambulation (Bandura, 2004). The ASCQ is a 22-item questionnaire where participants are asked to rate questions on a scale from 0 (not confident at all) to 10(extremely confident). (Asano et al., 2007). The ASCQ has been shown to have both reliability and validity in community-dwelling older adults (Asano et al., 2007).

**Timed Up and Go (TUG) Test.** The TUG assesses an individual’s ability to stand from a sitting position, walk three meters, turn around, walk back and sit back in the chair.87 It captures aspects of mobility capacity (what an individual can do)86 including sit-to-stand transitions, gait initiation, acceleration and deceleration, and turning.87

***Secondary outcomes*** are aligned with the performance objective of SMART and adults with LLA challenges (mentioned in section 1.2.) as well as patient-reported outcomes to capture patients’ views of their symptoms, and their functional status,61, 73 including:

- Physical Activity Identity (PAI) scale is a 9-item measure of an individual's identification with exercise as an integral part of the concept of self,38 with high test-retest reliability and good validity. We will use a modified version of the PAI questioning the extent that physical activity is considered a part of an individual’s aspect of self.74
- Activities Specific Balance Confidence Scale (ABC) isa 16-item self-reported measure of balance self-efficacy during ambulatory activities with total score of 0 to 100.40
- Euro Quality of Life – Five Level Instrument (EQ-5D-5L) assesses five dimensions of health-related quality of life: mobility, self-care, usual activities, pain/discomfort, and anxiety/depression.88
- Tenacious goal pursuit (TGP) assesses the tendency to persist and increase effort in pursuing goals facing obstacles.89
- Action planning scale (AP) assesses whether people had formed a plan which links goal-directed behavior to environmental cues by identifying when, where, and how to act.90 We will assess the AP for “exercising”, “skin monitoring”, and “cleaning the prosthesis”.
- Self-Management Assessment Scale (SMASc) assesses five domains that are important for an effective self-management, including “knowledge, goals for future, daily routines, emotional adjustment, and social support”.91
- *The Center for Epidemiologic Studies Depression Scale (CES-D)* is used to assess depressive symptoms over the past week in adults with LLL.92-94 Depression is an important health outcome in adults with LLL.
- *Revised Amputee Body Image Scale (ABIS-R)* assesses feelings about the body experienced after amputation.95,96 Poorer perceived body image is associated with depression and lower level of prosthetic satisfaction.97
- *Pain* is common in individuals with LLL and can adversely affect quality of life. We will assess the following: residual limb pain (pain in the remaining part of the amputated site); phantom limb pain (in missing part of the limb); and phantom sensation (in missing part of the limb). The intensity of pain and sensation in the past week will be assessed using a 10-cm visual analogue scale (VAS), ranging from 0 (which indicates no pain or sensation) to 10 (which indicates the worst pain or sensation possible).
- *Short Musculoskeletal Function Assessment (SMFA)* assesses individuals' perceived health status.98,99 The SMFA includes 46 items in three sections: difficulty with daily activities (items 1 to 25), experiencing problems because of injury (items 26 to 34), and the extent to which the person is bothered by the problems (items 35 to 46). In this study, we will use items 1 to 34, which cover the functional assessment.
- *Self-Report Habit Index (SRHI)* assessesthe automaticity of a behavior and the extent to which individuals with LLL have integrated self-management tasks into their self-concept.100,101 We will assess the habit formation for “skin monitoring” and “cleaning the prosthesis,” which are important in managing a LLL.

***Implementation:*** Following the [RE-AIM](http://www.re-aim.org/) framework,60 five elements of implementation will be assessed including, reach (target population), effectiveness (effects of SMART), adoption (by setting/staff), implementation (dose delivered and received, fidelity to the intervention), and maintenance of the behavior (in target population and settings). During study, the research coordinator will keep the detailed logs to monitor fidelity to research protocols and review the online chart for the adherence to the SMART (dose). Moreover, ***participant experience*** will be identifiedwith a brief30-minute audio-recorded semi-structured in-person interview with men and women (n=20) from the experimental group (*Section 2.2*) by the researcher at the end of the study (T3) to explore the experience and acceptability of the SMART program, health related goals, and any perceived disadvantageous of SMART. Moreover, we will call any dropout participants to obtain their feedback.

***Sociodemographic and Clinical Characteristics***: We will collect descriptive characteristics at T1 (**Appendix E**) including, age, sex, gender, level of education, marital status, weight, height, and clinical variables, such as presence of comorbidities, level, cause, side, and date of amputation, discharge date, date in which prosthetic training has been started, and date in which patient received the permanent prosthesis. We will also collect the participants’ self-report encounters with outpatient rehab care providers (e.g., PT, OT) and surgical consultations throughout the six-week intervention.

A cognitive screen, the Montreal Cognitive Assessment (MoCA) will be used to screen for cognitive impairments.

**2.9 Measuring outcomes at follow-up:** We will collectdata for intervention and control groups at three time points (**Appendix E**): T1=baseline; T2=within one week of completing SMART intervention; T3=retention period of four weeks post-intervention. The one-on-one semi-structured interviews with the SMART group to determine impressions of the protocol and intervention will be conducted at T3. All data collection will occur through online survey link on Qualtrics platform hosted by University of British Columbia. All sessions will be performed on Zoom video call.

**2.10 Sample Size:**Our sample size calculation is based on identifying SMART is more effective than standard care from a clinical point of view (Clinical Superiority design),75 and minimize any potential waste of resources.76 We are planning to compare the 2-MWT using a ratio 1:1. In a previous study, the mean (SD) of clinically important change in distance walked in 2 minutes at discharge from the rehab facility was 13.6 (19.9) m in adults with unilateral LLA (mean age = 66 y).37 Assuming minimum important difference of 13.6 m, we will need to enroll a minimum 34 participants per group to be enable to reject a null hypothesis of no difference in means of walking capacity between the 2 groups with 80% power. The type-I error probability associated with this 2-sided test of the null hypothesis is 0.05. Our sample size is based on the feasibility of recruiting 2 adults aged over 50 years with an LLA, per site within 18 months, and with 68 participants at final assessment (accounting for participant attrition) we can have enough power to detect a difference in the primary outcome, i.e., 2-MWT. Acknowledging the challenges with participants,77 20% attrition rate, and non-compliance rate in RCTs, we will recruit 82 participants (41 per arm including both men and women).The target sample size will also facilitate estimates for adherence, and the number of participants with certain covariates (e.g., sex, gender), and inform the sample size calculation and stratification for the implementation study.

**2.11 Health services research issues:** Cost and cost-effectiveness of eHealth interventions have been demonstrated for patients with chronic disease conditions.78 However, we will not do a formal cost analysis in this study.

**2.12 Recruitment:**We anticipate it will take 3 years to complete this study **(Fig. 2)**. Eligible candidates will be identified from the Toronto, London, and Vancouver amputee clinics, as well as hospitals in 4 additional British Columbia Health Authorities: Fraser Health, Interior Health, Northern Health, and Vancouver Island Health. Invitation to participate will be provided through letters of information sent electronically or verbally by clinicians at each facility. Volunteers will contact the research coordinator or provide their verbal permission to their clinician to share their contact information (name and email/phone #) with the research coordinator. Volunteers will be screened by telephone upon contacting the research coordinator with an expression of interest to participate in the study. Upon successful screening/enrollment and baseline data collection (T1) the *research coordinator* will log onto the online randomization system to determine the next allocation within 48 hours, then, participant contact information will be forwarded to the appropriate *group Trainer* **(Appendix E)**. To mitigate recruitment challenges, we will offer an honorarium of $25 dollars per data collection session (T1-T3) to both groups. An additional $25 will be given to SMART group participants who participate in the T3 qualitative interview.

**2.13 Compliance:**The trainer of the SMART group will monitor the activity of participants through a website and will contact the participant to inquire about reasons for inactivity and troubleshoot any problems including technical issues. We also will explore the acceptability of SMART with the qualitative component of the study. Control group subjects will receive weekly contact.

**2.14 Loss to follow-up:**To mitigate loss to follow-up study coordinators will maintain contact with participants once every 4 weeks until study completion in addition to the trainer contact. Use of this strategy in a prior study by Imam and **NPA** **[name]**, et al30 demonstrated <20% loss to follow up.

**2.15 Study Centers:**We will recruit 82 individuals, equating to 20 or 21 participants per site. Multiple sites were chosen to understand the diversity of LLA population and health services: In British Columbia, we will recruit from GF Strong and Holy Family Hospital in Vancouver, BC, where approximately 100 adults with new LLA receive care each year. Participants will also be recruited from hospitals in 4 additional British Columbia Health Authorities: Fraser Health, Interior Health, Northern Health, and Vancouver Island Health; Sunnybrook and West Park in Toronto, each with over 100 inpatients per year; and Parkwood Hospital in London, ON, where more than 75 older adults with new LLA receive care. Our community partner Barber Prosthetics ([name] and [name]) will assist with recruitment through their extensive network in Metro Vancouver (Burnaby to Hope).

[figure not shown]

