**H1.** walking capacity, operationalized as higher change score with the two-minute walk test;37

**H2.** physical activity identity, knowledge, self-efficacy, and falls confidence, operationalized as higher change score with the physical activity identity questionnaire,38 patient activation measure,39 and activities specific balance confidence scale.40

**Work completed to support this proposal:**We have completed a number of key feasibility and development studies to support this next phase of testing effectiveness of the innovation (SMART eHealth intervention) and describing its implementation. Using a participatory action research approach,1 we created a Steering Group with our clinical co-investigators (Co-applicants (Co-A) clinicians **[name], [name], [name] and [name]** and patient partners **[name], [name], [name])**. We met 8 times over two years. We co-created the SMART web-based app (please see **Appendix A**), designed to guide adults with LLA to actively engage in self-management. The app is asynchronously monitored through a website portal. There were 31 clinicians, and 26 adults with LLA (73% men) who engaged in semi-structured interviews to identify common themes in the recovery process, and app content to best augment existing LLA rehab. Key findings were: adults with LLA (i) requested tools and strategies to return to walking and independence in activities of daily living (ADLs); and (ii) perceived a new identity after amputation. This feedback was incorporated into the SMART intervention, for required content and the need for peer support to enact the principles of self-management.34, 36 In parallel, we conducted a systematic review and meta-analysis of telehealth interventions for patients with lower limb musculoskeletal surgery41 to identify effective behavior change techniques (BCTs)42, 43 to incorporate into SMART. Self-efficacy44 and action planning theory45 informed the development of SMART. We were also guided by the Theoretical Domains Framework46, 47 to incorporate relevant BCTs within SMART. For example, social support, instruction on how to perform the behavior, self-monitoring behavior, etc. We currently completing a pilot study with a mixed method approach to address design and SMART intervention fidelity with 10 participants who have lived with a LLA for at least 1 year.48

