**2.4 Protecting against bias - Blinding:**Blinding of participants for the RCTs on the effect of eHealth interventions is impossible because of nature of intervetnions.66 Therefore, it is difficult to blind participants to the intervention received. The assessors will be blinded to group allocation, we will complete the primary outcome (TUG and ASCQ) first, and participants will be asked not to disclose their group allocation during assessments.66 Furthermore, we will have separate trainers for each group (to minimize trainer bias); and the primary outcome measure, the TUG is a performance-based measure with standardized instructions. Finally, all statistical analyses will be conducted by a blinded statistician.

**2.5 Inclusion and Exclusion Criteria:**To be included, participants will: have a unilateral dysvascular- or diabetic- related LLA (transtibial or transfemoral);3have conducted the casting for their initial prosthetic limb (up to 2 years); be aged ≥ 50 years (85% of adults with LLA);3 have a computer or tablet and have access to the internet, and self-identify as being able to speak and read English. We will exclude adults with substantial health conditions (e.g., congestive heart failure, diagnosed dementia); those anticipating further surgery (e.g. LLA revision) as identified by our study sites’ physiatrists; and an ability to use a tablet (e.g./ using hands for typing). Given these criteria, the results of this study will not be generalizable to all adults with LLA such as the very young and those who do not speak English. As most people with LLA are >50 years old and more than 90% of the population of BC and ON speak English, we are confident of obtaining a representative sample.

**2.6 Duration of Intervention:**Participants in the SMART group will receive the intervention for six weeks. Participants in the control group will be contacted weekly for a similar 6 week period.

**2.7** **Frequency and Duration of Follow-up:**There are six weekly SMART modules with each taking approximately 20 to 30 minutes to complete. Individuals will be encouraged to complete one module a week to reduce any perceived burden, and gradually integrate the information. Participants from both groups will receive a weekly contact: SMART group participants will receive a 20 minute telephone call/Zoom video call from peers, and the Control group participants one email or phone call by trainer.

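### The sample size and 80% power claim in section 2.10, and hypothesis H1, are tied to the two-minute walk test, while sections 2.4 and 2.8 make the TUG (in one place TUG and ASCQ) primary, so the stated power does not belong to the defined primary outcome

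*Protocol*

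**What the plan says.** Three places in the protocol describe the main walking outcome, and they do not agree.

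- **Section 1.2, H1** specifies "walking capacity, operationalized as higher change score with the two-minute walk test". Research question Q1 in the same section asks about both walking confidence and walking capacity. H2 relies on three instruments, one of them the "patient activation measure".
- **Sections 2.4 and 2.8** use the TUG. Section 2.8 says of the walking outcome: "We operationalized this as the Timed Up and Go Test (TUG), a performance measure of walking capacity". Section 2.4 first says "we will complete the primary outcome (TUG and ASCQ) first", and a few lines later calls "the primary outcome measure, the TUG is a performance-based measure with standardized instructions". In 2.8 the ASCQ is described ahead of the secondary-outcomes heading.
- **Section 2.10** returns to the walk test: "We are planning to compare the 2-MWT using a ratio 1:1". It takes 13.6 m (SD 19.9 m) as the target, with two-sided alpha 0.05 and 80% power, and arrives at 34 per group. It closes with the statement that at 68 assessed participants "we can have enough power to detect a difference in the primary outcome, i.e., 2-MWT".

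The 2-MWT appears in neither the primary nor the secondary list of 2.8. The patient activation measure is not listed there either.

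**The concern.** A power statement holds for one outcome, with its own target difference and SD. Here it is made for a distance in metres, while the outcome defined as primary is a time in seconds, possibly joined by a questionnaire score. Neither of those has a planning difference or an SD in the protocol.

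Three things are at stake. The protocol claims 80% power that it has not shown for its defined primary outcome. The outcome for the confirmatory test is not uniquely fixed. And section 2.17 plans an interim analysis of the primary outcome that can stop the trial, without saying which measure that is.

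The text looks like an incomplete change of outcome. Section 2.8 says the TUG is used "with strong evidence of reliability, validity, and responsiveness.37, 70", but the reference list shows both of those sources to be titled as 2-MWT papers. The same paragraph argues from the ability to walk longer distances, which a 3-metre timed task does not record.

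**Working it through.** **1. Reproducing the protocol's figure.** Inputs, all from section 2.10: difference 13.6 m, SD 19.9 m, two-sided alpha 0.05, power 80%, ratio 1:1.

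n per arm = 2 × (1.960 + 0.842)² × (19.9 / 13.6)² = 33.6, rounded up to 34.

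This matches. Power at 34 per arm is 80.5% by the normal approximation and 79.3% by the t-test (which would need 35). The calculation is sound for the 2-MWT.

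**2. What carries over to another outcome.** Only the standardised difference does: 13.6 / 19.9 = 0.68. By the normal approximation, the difference detectable with 34 per arm is (1.960 + 0.842) × √(2/34) = 0.68 SD; by the noncentral t it is 0.69 SD. The protocol gives nothing with which to turn this into seconds on the TUG or points on the ASCQ.

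**3. Power at 34 per arm over a range of effects.** The d values are assumptions, not protocol figures (t-test, two-sided 0.05, no baseline adjustment).

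| Assumed d | Power at 34 per arm | n per arm for 80% power |
|---|---|---|
| 0.3 | 23% | 176 |
| 0.4 | 37% | 100 |
| 0.5 | 53% | 64 |
| 0.6 | 68% | 45 |
| 0.8 | 90% | 26 |

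**4. Effect of the planned ANCOVA.** Section 2.16 adjusts for the baseline score. With baseline correlation r, the detectable d is multiplied by √(1 − r²). The values of r are assumptions.

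| r | Detectable d, 34 per arm |
|---|---|
| 0.5 | 0.69 × 0.866 = 0.60 |
| 0.7 | 0.69 × 0.714 = 0.49 |
| 0.8 | 0.69 × 0.600 = 0.41 |

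**5. Expected completers.** Section 2.10 recruits 82 and allows for 20% attrition: 82 × 0.80 = 65.6, about 66, or about 33 per arm. The unadjusted detectable d is then 0.70. The difference from 34 per arm is small.

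**6. If the TUG and ASCQ are both primary.** If each is tested at 0.05 and success on either counts, the familywise error is up to 1 − 0.95² = 9.75% under independence. With each tested at 0.025, power at d = 0.5 and 34 per arm falls from 53% to 41%.

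**The case against.** The best defence is that the trial may still be adequately sized. The number 34 per arm is correct arithmetic, a standardised difference of 0.68 may be a fair target on the TUG too, and ANCOVA on baseline is already planned and would bring the detectable difference down. That stands as far as it goes: nothing in the protocol shows an actual shortfall. It does not rescue the power statement, because the protocol never makes that argument for the TUG and gives no figures from which to make it. Nor is this detail left to an SAP, since the protocol itself makes the claim and attaches it to a different outcome.

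A reader might infer more than the document supports on several points.

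- *That the 2-MWT is not measured at all.* Only its absence from the text of 2.8 is established. Section 2.10 still plans to compare it, and the Appendix E flowchart is a figure that is not shown.
- *That a null TUG result would be uninterpretable.* It would not be. The confidence interval for the TUG difference shows which effects are excluded, whatever the planning calculation was.
- *That H1 has the wrong sign.* As written it concerns a distance, where a higher change is the right direction. The direction needs attention only if H1 is moved to the TUG.
- *That 13.6 m is wrongly used as a between-arm difference.* Section 2.10 labels it a minimum important difference. Whether that label is right depends on a cited source that is not available here.
- *That the TUG has no measurement support.* Section 2.8 separately cites a TUG study in amputees for reliability and validity. Only the responsiveness claim rests on 2-MWT papers.
- *That the 10-person pilot can supply the TUG SD.* Nothing in section 1.2 says it measured the TUG, and its participants had lived with an amputation for at least a year.

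**Conclusion.** The point holds as an internal contradiction with a direct consequence for the power claim. Section 2.10 and H1 use the 2-MWT; section 2.8 uses the TUG; section 2.4 uses the TUG and ASCQ, then the TUG alone. The 80% power therefore does not apply to the primary outcome or outcomes as defined in 2.4 and 2.8. Correcting 2.10 for the TUG alone would not be enough while 2.4 also names the ASCQ and Q1 asks about confidence, because a second named primary outcome would remain without a power statement.

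The size can be given only in standardised units: about 0.69 SD detectable at 34 per arm without adjustment, about 53% power at 0.5 SD, and 0.41 to 0.60 SD detectable with adjustment if the baseline correlation lies between 0.8 and 0.5. The effects and correlations are assumptions. Whether 82 participants are enough for the TUG or ASCQ cannot be decided from the protocol in either direction.

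As a lesser matter, H2 cannot be tested in full with the outcomes listed, because the patient activation measure is not in 2.8.

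**What to change.** 1. Reconcile sections 1.2, 2.4, 2.8 and 2.10 on one named primary outcome, or on the TUG and ASCQ as co-primaries with a stated multiplicity rule. Name the same outcome(s) for the interim analysis in 2.17.
2. In 2.10, replace the 2-MWT power claim with the difference detectable at 80% power for the chosen outcome(s) under the planned ANCOVA, at 82 recruited and about 66 completers. Show it over a stated range of SD and baseline correlation, with the source of each.
3. If the TUG is primary, restate H1 as a greater reduction in TUG time, and replace or remove the 2-MWT citations given for responsiveness. If the ASCQ is also primary, add it to the hypotheses; neither H1 nor H2 mentions it now.
4. If the 2-MWT is still meant to be primary, list it in 2.4 and 2.8 instead; the calculation in 2.10 then applies to it.
5. In H2, replace the patient activation measure with an instrument listed in 2.8, or add it to 2.8.

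The cost is protocol wording and one recalculation. Restating the power adds no participants in itself, but it may look less favourable than the present 80%.

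### At the stated 20% attrition, 82 recruits leave about 66 completers, not the 68 that section 2.10 requires; the power cost is about 1.5 points

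*Protocol*

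**What the plan says.** Protocol section 2.10 (Sample Size) sizes the trial on the 2-minute walk test (2-MWT): "We are planning to compare the 2-MWT using a ratio 1:1". The planning difference and standard deviation come from one earlier study, in which the change "at discharge from the rehab facility was 13.6 (19.9) m in adults with unilateral LLA". With that difference, a two-sided 5% test and 80% power, the protocol concludes: "we will need to enroll a minimum 34 participants per group".

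It then treats 68 as the number who must still be present at the end, stating that power is adequate "with 68 participants at final assessment (accounting for participant attrition"). The recruitment target follows in the next sentence, where the protocol acknowledges a "20% attrition rate, and non-compliance rate in RCTs, we will recruit 82 participants", 41 in each arm. No inflation formula is given and no rate is attached to non-compliance. Section 2.15 (Study Centers) repeats the 82.

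**The concern.** Section 2.10 gives three figures: 68 completers required, 20% lost, 82 recruited. Any two of them fix the third, and the three stated values are not compatible. If 20% are lost, the trial ends below its own minimum per group.

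The likely cause is a common slip: adding 20% to the required number instead of dividing by the 80% expected to remain. The same sentence also names non-compliance, so a reader may believe that the 82 contains a margin for it, when it does not fully cover attrition. At stake are a stated completer number and power that the plan does not quite reach under its own assumption, and a method that would repeat the error if the sample size were recalculated.

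**Working it through.** **Inputs, all from section 2.10.** Difference δ = 13.6 m; SD σ = 19.9 m; two-sided α = 0.05; power 80%; allocation 1:1; 34 per group; 68 at final assessment; attrition 20%; 82 recruited (41 per arm).

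**Step 1: reproduce the 34 per group.** Normal approximation for two means:

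n = 2 × [σ(z₀.₉₇₅ + z₀.₈₀)/δ]² = 2 × [19.9 × (1.960 + 0.842)/13.6]² = 33.61, rounded up to 34.

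This matches the protocol exactly, so the normal approximation is taken to be its method.

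**Step 2: reproduce the 82.**

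- Multiplying: 68 × 1.2 = 81.6, giving 82; per arm 34 × 1.2 = 40.8, giving 41. Both stated figures are reproduced.
- Dividing: 68/(1 − 0.20) = 85; per arm 34/0.8 = 42.5, giving 43, so 86 with equal arms. Neither stated figure is reproduced.

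That multiplication was used is an inference from this match.

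**Step 3: what 82 recruits leave.**

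- Completers at 20% attrition: 82 × 0.8 = 65.6, or 41 × 0.8 = 32.8 per arm.
- Largest attrition that still leaves 68: 1 − 68/82 = 0.171, or 17.1%.

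**Step 4: the effect on power.** By the normal approximation, power = Φ(δ/[σ√(2/n)] − 1.96):

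- n = 34: Φ(2.818 − 1.960) = 80.5%
- n = 32.8: Φ(2.768 − 1.960) = 79.0%

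The noncentral t, with the same δ and σ and 2n − 2 degrees of freedom, gives:

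| Completers per arm | Normal approximation | Noncentral t |
| --- | --- | --- |
| 34 | 80.5% | 79.3% |
| 33 | 79.3% | 78.1% |
| 32.8 | 79.0% | 77.8% |
| 32 | 78.0% | 76.8% |

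Going from 34 to 32.8 per arm costs 80.5 − 79.0 = 1.5 points by one method and 79.3 − 77.8 = 1.5 points by the other. The remaining gap of about 1.2 points between the columns is the difference between the two methods and has nothing to do with attrition.

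**Step 5: what baseline adjustment could recover.** Section 2.16 plans an ANCOVA adjusting for baseline score. If the baseline has correlation r with the analysed outcome, the residual SD is 19.9 × √(1 − r²). The protocol gives no r, so the values here are assumptions. At 32.8 per arm the noncentral t power is 77.8% for r = 0, 79.4% for r = 0.2, 80.4% for r = 0.25 and 81.5% for r = 0.3.

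**The case against.** The best defence is that the slip hardly matters. By the formula that produces the protocol's 34, expected power is still about 79%, and a one-point shortfall is minor beside the uncertainty of an SD taken from a single earlier study. This stands, and it sets the weight of the point. A reader might infer that the trial fails to deliver its 80% power in any serious sense, or that attrition alone takes it down to 77% to 78%. The documents do not support that: those lower figures come from switching to a t test, under which the protocol's own 34 per arm already gives only 79.3%.

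Second, the planned ANCOVA may recover the loss. It may, with a correlation of about 0.25, but section 2.10 neither claims this gain nor states a correlation. The intention-to-treat analysis with multiple imputation in section 2.16 likewise means that completers are not the only analysed set, but section 2.10 counts participants at final assessment, and the per-protocol analysis of completers is listed first.

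Third, section 2.14 reports loss below 20% with the same retention strategy in a prior study. That makes 20% look cautious, but it does not establish 17.1% or less, and section 2.10 plans on 20%.

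Fourth, non-compliance is only acknowledged, with no rate, so to say that the protocol claims to cover it may read too much into the sentence. That is fair. Still, it stands as a reason for the 82, and no allowance for it is left.

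**Conclusion.** The inconsistency is certain, because it follows from the protocol's own numbers: 20% attrition from 82 leaves about 66, about 33 per arm, against a stated minimum of 34. The recruitment figure consistent with 68 completers is 85, or 86 with equal arms, which is 3 or 4 more than planned; the attrition consistent with 82 is 17.1%. The explanation, multiplication by 1.2, is inferred.

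The consequence is small: about 1.5 points of power by either method, before any gain from baseline adjustment. This rests on the planning values of 13.6 m and 19.9 m and on equal loss in the two arms. It is a figure to correct and not a threat to the validity of the trial.

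One limit applies to every power figure here. They are for the 2-MWT, whereas sections 2.4 and 2.8 name the Timed Up and Go test (TUG) as primary, with section 2.4 adding the Ambulatory Self-Confidence Questionnaire. Correcting the attrition step does not turn them into power for the current primary outcome.

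**What to change.** Keep 82 and restate section 2.10 along these lines: *With 82 recruited and 20% attrition, about 66 participants are expected at final assessment, giving about 79% power (normal approximation; about 78% by t test) for the 2-MWT under the planning assumptions, before any gain from baseline adjustment. The 68 completers are reached if attrition is 17% or less.*

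Remove the implication that the 82 also allows for non-compliance. If a gain from ANCOVA is to be credited, state the assumed baseline correlation and its source. In any recalculation for the current primary outcome, divide the required number of completers by one minus the attrition rate.

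The cost is a change of wording and a slightly less favourable stated power. No participants are added and the timeline is unaffected. If the sponsor prefers to hold 68 completers at 20% attrition, the alternative is to recruit 85, or 86 with equal arms, and to update section 2.15 to match.
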